All participants will begin the study on the same, fixed date when their shift work begins (date to be finalized in January 2011). Since data collection will be electronic via the internet, study participants are expected to have internet access. If participants know they will not have internet access or reliable access, arrangements will be made to give them either paper or offline electronic data collection forms (as well as a pre-paid envelope to send the forms back in).

- - 1. STUDY VISITS, phone calls and email reminders

In addition to the initial study visit and phone calls described in section 5.1.1., the project coordinatorwill phone each subject within 3 days of the study start to review study procedures and outcome assessment documentation procedures. At this time, the project coordinator will inquire about effectiveness of the blind and about participant beliefs about medication effectiveness. The next call from the project coordinator to participants will occur during the 2nd week of the study (days 14 to 20) inquire about adverse effects and to remind them of completion of the outcome assessment forms to be filled out~~.~~ The project coordinator will call study participants during the 5th week of the study (days 35 to 41) to remind them of the forms to be filled out, inquire about adverse effects and schedule a follow-up visit for when they are finished their clinical rotation at the end of 10 weeks. Throughout the study, subjects will also receive daily email reminders containing a link to the online data collection forms for that day. At the 10-week mark (day 70), participants will be sent an email reminder to complete all outcomes assessment forms for the final time. At this time, they will again be queried about their thoughts on effectiveness of the study medication. They will then return any unused study medication to the study nurse during their final scheduled visit.

1. trial INTERVENTIONS

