**The following interventions will be supplied:**

1. ***Rhodiola rosea* extract standardized to2.8% rosavins (**29.0 % microcrystalline cellulose, 0.5% Silicon dioxide
2. **Placebo (**95% microcrystalline cellulose, 0.5% Silicon dioxide)

**Both interventions will be encapsulated in gelatine capsules, which are an animal-based product, and will look identical. Medications will be packaged in identical bottles labelled according to the participants’ randomization code.**

Development of the both interventions will be undertaken by [name] [name], a pharmacist and assistant professor in the Faculty of Pharmacy and Pharmaceutical Sciences at the University of Alberta. [name], will store all trial medications (*R. rosea* and placebo) in a secured storage facility until recruitment. Study medication will then be given to the study nurse for dispensing at time of enrolment; medication will be stored under lock and key accessible only by the study nurse until time of dispensing.

- 1. Treatment regimen

The trial will begin on the day that subjects start their clinical rotations and end 6 weeks later. Subjects will be instructed to take two to four capsules of the trial medication per 24 hour period (see section 6.2). All outcomes will be measured at baseline (Day 0) and at the end of the trial period (week 6). The project coordinator will phone participants on the day(s) leading up to their baseline assessment to remind them to complete their questionnaires and ensure they are comfortable with the study procedures. The primary outcome and two secondary outcomes will be measured again at the end of each week; all other outcomes will be measured daily (see section 7). Subjects will be prompted to report adverse events daily during the trial period and at the end of their clinical rotation four weeks after completion of the trial. During the trial period, the study nurse will phone participants in week 2 and week 5to remind them to complete their questionnaires and to inquire about adverse events (see section 7.1.2).

- 1. DOSE AND DURATION

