**The code for a patient will only be opened in an emergency, when it is necessary for a patient’s treatment to be disclosed. If a code is broken the investigator will inform the Study Director/Monitor and document the details of the reason in the patient’s case report forms.**

- 1. ALLOCATION CONCEALMENT

Participants will receive a sealed, serially-numbered opaque bottle containing the study medication or placebo depending on their randomised group assignment. They will be provided a six-week supply of their assigned study medication.

- 1. BLINDING

**The placebo capsule will have the same appearance, volume, weight, odour and taste as the *R.rosea* product so that neither the participant nor trial personnel know who is receiving which medication. The effectiveness of the blind will be assessed at the beginning of the study after a single dose via the MYMOP on Day 1. Participants will be asked to guess which medication they think they were allocated to.**

- 1. **CO-INTERVENTION AND CONTAMINATION**

**Since stimulant medications have been identified as potentially hazardous to combine with *R.rosea*, subjects being recruited will be considered ineligible for the trial if they are using such medication. As part of their daily questionnaires, participants will be asked to record any medication used (prescription, over-the-counter, or natural health product) and quantity of caffeine and alcohol consumption in the past 24 hours to ensure that important co-variables can be considered in the final analysis. These questions will be administered as part of the daily MYMOP assessment.**

**From the start of the treatment, participants will be advised not to take any rhodiolaor ginseng preparations for the duration of the trial so that only the *R. rosea* treatment will influence trial outcomes. Furthermore, they will be informed that there is a 50% that they may be receiving *R.rosea*, the dose of which is being in this trial is the highest that has been supported by evidence of safety, and cautioned that they would therefore not want to “double-dose” themselves.**

- 1. **ACCOUNTABILITY OF TRIAL MEDICATION**

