1. OUTCOME MEASURMENT

**Measurements for all outcomes will be collected using an online data collection and management system. Participants who will not have regular internet access during the trial period will be given paper forms to fill out and be asked to return the forms by prepaid mail or in-person at the end of the trial period.**

- - 1. PRIMARY OUTCOME

No clear definition or measurement tool for fatigue exists. The main limitation of fatigue scales is that very few have evidence indicating what constitutes a minimum clinically important difference (MCID) or a reference score for the target population. As such, the vitality subscale of the generic health-related quality of life instrument, RAND-36, will be employed to assess fatigue. The instrument will be administered at baseline, the end of each week (days 7, 14, 21, 28, 35, and 42). Since the vitality scale is not specifically validated for measuring fatigue, a Visual Analogue Scale for Fatigue (VAS-F) (44) will be concurrently administered so it can be compared to the vitality subscale since the VAS-F has proven validity in fatigued and healthy populations (45).

- - 1. SECONDARY OUTCOMES

1. ***Health-related quality of life:*** The RAND-36 is a 36-item questionnaire that assesses eight areas of functioning: physical functioning, role limitations caused by physical health problems, role limitations caused by emotional problems, social functioning, emotional well-being, vitality, and general health perceptions. This questionnaire will be assessed concurrent to the primary outcome (baseline, days 7, 14, 21, 28, 35 and 42) since the vitality subscale is a subset of this questionnaire.
2. ***Individualized outcomes:*** Since fatigue is subjective, and its impact is highly variable between individuals, individualized improvement will be measured using the Measure Yourself Medical Outcomes Profile (MYMOP). This tool will be used to measure change in items of importance to the participant, as identified by the participant. Participants will be asked to complete this short survey daily. Additional questions regarding concurrent medication and sleep hours/quality will be included on the MYMOP. On MYMOP for Day 1, participants will be probed as to their beliefs about which medication they have received in order to test the effectiveness of blinding.

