   1. ***Beliefs about efficacy:*** At the beginning of the study, simultaneous to testing the effectiveness of the blind on day 1, participants will be asked how likely they think *R. rosea* is to be effective for fatigue. Participants will be asked the same question at the end of the study.
3. ***Adaptive capacity:*** The Adaptive Capacity Index (ACI) is a 21-item questionnaire that is intended to measure a subjects’ ability to adapt to stressors. The measure has recently been developed and this study aims to provide additional psychometric data about the measure. It is a self-reported measure comprised of five subscales measuring muscle endurance, cognitive function, sleep quality, emotional reactivity and social interaction. It will be administered on the same schedule as the primary outcome.

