  - is a congenital anomaly/birth defect.

A serious adverse event will result in withdrawal from the trial.

On the third study call, the study nurse will schedule a visit with subjects for the end of their 10-week clinical rotation. During that visit subjects will be asked to return all unused study medication, queried about occurrence of any adverse events after the end of the study period and asked about the effectiveness of study medication.

- - 1. WITHDRAWALS/Stopping rules

Due to the implied high prevalence of fatigue among nurses on shift-work, and anticipated low-risk of side-effects, a high rate of participant withdrawals is not expected. Nonetheless, a 40% drop-out rate has been accommodated in the sample size calculation.

Some participants may choose to withdraw from the study. Reasons for withdrawal will be documented as one of the following:

- Adverse Event (serious or not)
- Death
- Withdrawal of consent
- Protocol violation
- Treatment failure or insufficient response
- Lost to Follow up
- Other

Up to 2 attempts to contact participants who are lost to follow-up will be made by phone or email. Patients who withdraw from the study will be encouraged to undergo all outcomes assessments listed for the final follow-up session.

Those participants, who meet any of the exclusion criteria during the trial, will be withdrawn.

Since there will be no interim analysis performed, there are no stopping rules for the entire trial (i.e. for harm, benefit or lack of overall benefit of the intervention).

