All primary analyses will apply the intention to treat principles. All statistical tests are two-sided and tests will be evaluated against 0.05 level of significance. Estimates and corresponding 95% confidence intervals will be reported. The RAND-36 vitality subscore will be used as the primary indicator of the efficacy of *R.rosea*. To test the main hypothesis of the effects of *R.rosea* in reducing fatigue of nurses involved in shift work, the mean change from baseline to six weeks of the vitality subscore using RAND-36 will be compared between the *R.rosea* and placebo groups. This 2-sample t-test will be supplemented by additional analyses using rate of change outcome measure. Linear mixed model will be employed to test changes in the intercept and slopes of the treatment groups. This type of modelling accounts for the variability and correlatedness of the observations on the same participant. Despite the tendency of participants to miss testing occasions, the mixed model analyses can still evaluate any trajectories of change. Missing data will be checked for randomness and correlation with adverse events will be explored. Since RAND-36 vitality subscore is not validated for use in this specific population, correlatedness between it and a visual analogue scale for fatigue (VAS-F) will be tested. In addition, correlatedness between ACI, will be tested against the primary outcomes in order to establish further evidence of validity. RAND-36 physical and mental component scores will be analysed by testing their mean change from baseline to day 42 between treatment groups, as a secondary outcome. Mixed model analyses will be applied for testing change for VAS-F, RAND-36, ACI and MYMOP. Side by side graphs of the rates of change between treatment groups will be plotted at the exploratory and final stages of analysis. Examination of the effect of the covariates - concurrent medication, dose-related change, sleep, alcohol use and impact of specific rotation (rotating vs permanent shift-work), age and marital status will be analyzed using linear mixed regression models as secondary outcomes. SAS 9.1 (Cary, N.C.) will be used for data management and statistical models. SPSS (Michigan) or Splus/ R will be used for supplemental graphs.

Adverse events will be monitored daily. Rates of adverse events will be compared between the two groups using the chi squared test at baseline, day 21 and day 42 measurements.

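### Outcome forms are due at day 70 in section 5.1.2 but stop at day 42 in sections 6.1 and 7, so an off-treatment value could enter the slope models and the final assessment of withdrawals has no clear date

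*Protocol*

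**What the plan says.** Section 5.1.2 (study visits, phone calls and email reminders): "At the 10-week mark (day 70), participants will be sent an email reminder to complete all outcomes assessment forms for the final time".

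The other sections stop four weeks earlier:

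- Section 6.1 (treatment regimen): "The trial will begin on the day that subjects start their clinical rotations and end 6 weeks later", and "All outcomes will be measured at baseline (Day 0) and at the end of the trial period (week 6".
- Section 7.1.1 (primary outcome, RAND-36 vitality): "The instrument will be administered at baseline, the end of each week (days 7, 14, 21, 28, 35, and 42". The rest of RAND-36 follows the same days (section 7.1.2).
- Section 7.1.2, Adaptive Capacity Index (ACI): "It will be administered on the same schedule as the primary outcome".
- For the end of the rotation, section 6.1 names only adverse-event reporting. Section 7.1.2 names return of medication, adverse events and perceived effectiveness. Neither names outcome forms.

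Medication covers six weeks only (section 6.4): "They will be provided a six-week supply of their assigned study medication".

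Section 8.2 fixes the primary t-test at change from baseline to six weeks, and the RAND-36 component scores at change from baseline to day 42. It then adds: "Linear mixed model will be employed to test changes in the intercept and slopes of the treatment groups". Mixed models are also planned for VAS-F, RAND-36, ACI and MYMOP. No time window is given for any of them.

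On participants who leave early, section 7.1.3 says: "Patients who withdraw from the study will be encouraged to undergo all outcomes assessments listed for the final follow-up session".

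**The concern.** The coordinator and the data team cannot follow both schedules. Either efficacy forms exist at day 70 or they do not, and the protocol says both. If they do exist, two things follow.

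First, the slope models are meant to describe change under treatment. A straight line through seven on-treatment weekly values and one value four weeks after the supply has ended estimates something else, and the isolated late point has high leverage.

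Second, section 5.1.2 uses follow-up visit and final visit for week 10. A reader applying section 7.1.3 could therefore ask withdrawn participants for outcome data at week 10 and not at week 6. A week-10 value cannot supply the six-week change in the primary comparison, and someone might be tempted to substitute it. The analysis is by intention to treat and the sample size allows for 40% drop-out, so the timing of withdrawal data matters here.

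**Working it through.** **1. Dates.** Week 10 = 10 × 7 = day 70; week 6 = 6 × 7 = day 42. 70 − 42 = 28 days = 4 weeks. This reproduces section 6.1, which puts the end of the rotation four weeks after the end of the trial period. Day 70 is therefore off treatment.

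**2. Schedules side by side.**

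| Place | Outcome forms at day 42 | Outcome forms at day 70 |
|---|---|---|
| 5.1.2 | not mentioned | all, as the last collection |
| 6.1 | all outcomes | none (adverse events only) |
| 7.1.1 and 7.1.2 | last listed day for RAND-36 and ACI | none listed |
| 8.2, t-test and component scores | end point | not used |
| 8.2, mixed models | window not stated | window not stated |
| 7.1.3, withdrawals | session not dated | session not dated |

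**3. Illustration: slope for a weekly instrument.** From the protocol: the target difference of 6.5 points (section 8.1) and the visit days. Assumed, because the protocol does not give them: the group difference rises linearly from 0 to 6.5 over days 0-42, and 100%, 50% or 0% of it remains at day 70.

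Slope b = Sxy / Sxx, where Sxx = Σ(t − t̄)² and Sxy = Σ(t − t̄)y. With balanced times this equals the random-intercept estimate.

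- Days 0, 7, …, 42: t̄ = 21, Sxx = 1372, Sxy = 212.33. b × 42 = 6.50.
- With day 70 added: t̄ = 27.125, Sxx = 3472.9.
  - 100% persists: Sxy = 351.68, b × 42 = 4.25 (65% of 6.50).
  - 50% persists: Sxy = 212.33, b × 42 = 2.57 (40%).
  - 0% persists: Sxy = 72.99, b × 42 = 0.88 (14%).

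The day-70 point alone contributes (70 − 27.125)² / 3472.9 = 1838.3 / 3472.9 = 53% of Sxx.

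As a check on the correlation model, AR(1) weighting with weekly correlation 0.5 or 0.8 gives 62% or 61% of the on-treatment slope at full persistence, 33% or 31% at half, and 4% or 2% at none. The direction is the same.

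**4. Power of the slope test.** Further assumptions: 64 is read as the total, so n = 32 per arm. SD = 7.9 is the value at which a two-sample t-test with 32 per arm has 90% power for 6.5. Residual variance is half the total, 7.9² / 2 = 31.2. The model has a random intercept only.

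SE(b) = √[(2/n) × 31.2 / Sxx], and power ≈ Φ(b/SE − 1.96).

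- Days 0-42: SE × 42 = 1.58; 6.50 / 1.58 gives z = 4.10; power 98%.
- With day 70: SE × 42 = 0.995.
  - 100%: z = 4.27, power 99%.
  - 50%: z = 2.58, power 73%.
  - 0%: z = 0.89, power 14%.

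**5. Daily MYMOP.** With daily values on days 0-42 plus day 70, t̄ = 22.11, Sxx = 8968.4, and day 70 contributes 26% of Sxx. In the same scenario the slope per 42 days is 5.53, 4.80 or 4.07. MYMOP has its own scale, so these are best read as shares of the on-treatment slope: 5.53/6.50 = 85%, 4.80/6.50 = 74%, 4.07/6.50 = 63%.

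**The case against.** The strongest reply is that the analysis that matters is already safe. Section 8.2 ties the primary t-test to six weeks and the component scores to day 42, so a day-70 form cannot move either in a participant who completes. That stands. A reader might infer that the primary result is compromised; for completers the protocol does not support this.

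A second reply is that the window of a supplementary model is normally set in the SAP, which is not at hand, and that a model introduced as a supplement to a six-week t-test would naturally share its window. This also stands: the missing window is not itself an error. It is tempting to say that the day-70 value enters the slopes, but no section says so. What remains is that the protocol gives two data-collection schedules. A SAP can choose a window, but it cannot settle which schedule was carried out.

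Third, section 7.1.3 names a set of assessments and not a date, and could mean completing that set on leaving. Section 7.1.2 lists no outcome forms at the week-10 visit. So the stronger reading, that withdrawals are assessed at day 70, is plausible but not stated. The defect is that the session is undated and the nearest use of the term points to week 10.

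Finally, the figures rest on assumptions the protocol does not make, including the random-effects structure. Power does not fall if the effect fully persists, and the near-zero slope belongs only to the weekly instruments with no persistence.

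**Conclusion.** The contradiction is real and lies in the protocol's own text: section 5.1.2 collects all outcome forms at day 70, while sections 6.1 and 7 stop at day 42. It does not affect the primary t-test or the component scores in completers. It leaves the slope models for vitality, VAS-F, RAND-36, ACI and MYMOP open to an off-treatment value, and leaves the assessment of withdrawals open to a date that cannot serve the six-week comparison.

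The size depends on how much effect persists after treatment, which is unknown. For weekly instruments the slope keeps between 65% and 14% of its on-treatment value, and for daily MYMOP between 85% and 63%. For the weekly instruments the slope falls even at full persistence, where power is unchanged or slightly higher. Serious loss of power needs a substantial part of the effect to fade. These figures are a range under the stated assumptions, not a forecast. The point should be corrected, as a matter of consistency with a possible analytic consequence.

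**What to change.** Give one outcome schedule across sections 5.1.2, 6.1, 7 and 7.1.3, stating plainly whether outcome forms are completed at day 70.

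If day 70 is dropped, limit the week-10 contact to what sections 6.1 and 7.1.2 already list. If it is kept, add it to section 7 as off-treatment follow-up, and state in section 8.2 that the efficacy slopes use days 0-42, or that the off-treatment period is modelled as a separate segment. Either choice removes the problem.

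In section 7.1.3, replace the undated session with the day-42 outcome assessment, so that withdrawn participants are asked for data at the primary time point.

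The cost is a few sentences. No visit is added, the sample size does not change, and any day-70 data can still be collected and reported.

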**The following interventions will be supplied:**

1. ***Rhodiola rosea* extract standardized to2.8% rosavins (**29.0 % microcrystalline cellulose, 0.5% Silicon dioxide
2. **Placebo (**95% microcrystalline cellulose, 0.5% Silicon dioxide)

**Both interventions will be encapsulated in gelatine capsules, which are an animal-based product, and will look identical. Medications will be packaged in identical bottles labelled according to the participants’ randomization code.**

Development of the both interventions will be undertaken by [name] [name], a pharmacist and assistant professor in the Faculty of Pharmacy and Pharmaceutical Sciences at the University of Alberta. [name], will store all trial medications (*R. rosea* and placebo) in a secured storage facility until recruitment. Study medication will then be given to the study nurse for dispensing at time of enrolment; medication will be stored under lock and key accessible only by the study nurse until time of dispensing.

- 1. Treatment regimen

The trial will begin on the day that subjects start their clinical rotations and end 6 weeks later. Subjects will be instructed to take two to four capsules of the trial medication per 24 hour period (see section 6.2). All outcomes will be measured at baseline (Day 0) and at the end of the trial period (week 6). The project coordinator will phone participants on the day(s) leading up to their baseline assessment to remind them to complete their questionnaires and ensure they are comfortable with the study procedures. The primary outcome and two secondary outcomes will be measured again at the end of each week; all other outcomes will be measured daily (see section 7). Subjects will be prompted to report adverse events daily during the trial period and at the end of their clinical rotation four weeks after completion of the trial. During the trial period, the study nurse will phone participants in week 2 and week 5to remind them to complete their questionnaires and to inquire about adverse events (see section 7.1.2).

- 1. DOSE AND DURATION

**Each *R.rosea* capsule will contain 182.0 mg of the product.** Participants will be asked to take two capsules of the trial medication at the start of their wakeful period each day. Since fatigue is a subjective symptom, participants will be asked to self-determine their need for a second dose of the trial medication within the four hour period after the initial dose. The second dose willbe one capsule~~;~~ the daily MYMOP will ask participants to record the number of capsules ingested in the past 24 hours.

***Dose & duration justification:*** Since the majority of previous trials that found significant effects assess long-term, rather than acute supplementation of *R. rosea*, this trial will examine efficacy over a similar duration yet with an aim to overcome limitations of previous studies. **Based on dose and duration information previous studies of** R. rosea **for mental and physical performance (Table 2), the maximum dose of** R. rosea **without adverse effects is 1500 mg over three days (short-term supplementation). The maximum dose that has been safely used in long-term supplementation is 680 mg standardized to 3.0% rosavins for a six week period. The *R.rosea* formulation being used in this trial has been standardized to contain 2.8% rosavins; therefore the equivalent maximum daily dose for this study is 546 mg.**

- 1. **Treatment allocation**

**Partcipants will be assigned to a treatment group (either *R.rosea* or placebo) according to a computer generated randomisation scheme produced by our data management team at the Epidemiology Coordinating and Research Centre at the University of Alberta.** Sampling will be stratified by night vs. rotational shift workers and a permuted block randomization technique will be used with permuted block sizes of 4. Although the nursing profession is dominated by females, there has been no consistent association between fatigue and gender and therefore randomization will not be stratified by gender.

**The Investigator will be supplied with individual code-break envelopes for each patient, containing details of the patient’s treatment. Sealed copies of the randomisation code will also be retained by the study pharmacist, [name]** [name]**.**

**The code for a patient will only be opened in an emergency, when it is necessary for a patient’s treatment to be disclosed. If a code is broken the investigator will inform the Study Director/Monitor and document the details of the reason in the patient’s case report forms.**

- 1. ALLOCATION CONCEALMENT

Participants will receive a sealed, serially-numbered opaque bottle containing the study medication or placebo depending on their randomised group assignment. They will be provided a six-week supply of their assigned study medication.

- 1. BLINDING

**The placebo capsule will have the same appearance, volume, weight, odour and taste as the *R.rosea* product so that neither the participant nor trial personnel know who is receiving which medication. The effectiveness of the blind will be assessed at the beginning of the study after a single dose via the MYMOP on Day 1. Participants will be asked to guess which medication they think they were allocated to.**

- 1. **CO-INTERVENTION AND CONTAMINATION**

**Since stimulant medications have been identified as potentially hazardous to combine with *R.rosea*, subjects being recruited will be considered ineligible for the trial if they are using such medication. As part of their daily questionnaires, participants will be asked to record any medication used (prescription, over-the-counter, or natural health product) and quantity of caffeine and alcohol consumption in the past 24 hours to ensure that important co-variables can be considered in the final analysis. These questions will be administered as part of the daily MYMOP assessment.**

**From the start of the treatment, participants will be advised not to take any rhodiolaor ginseng preparations for the duration of the trial so that only the *R. rosea* treatment will influence trial outcomes. Furthermore, they will be informed that there is a 50% that they may be receiving *R.rosea*, the dose of which is being in this trial is the highest that has been supported by evidence of safety, and cautioned that they would therefore not want to “double-dose” themselves.**

- 1. **ACCOUNTABILITY OF TRIAL MEDICATION**

During the final visit with the study nurse at the end of their clinical rotation, subjects will be asked to return all unused study medication, including all packaging. The study nurse will return all unused medications to [name]. [name] will maintain an inventory, which will include details of receipt, dispensing, return and collection of the study medication.

